### Methods in analysis to handle protocol non-adherence and any statistical methods to handle missing data {20c}

We expect the number of withdrawals to be low because the intervention is not invasive and does not increase the risks of the standard procedure. Additionally, all the data will be collected during the visit in the plaster room; there is no follow-up, which will also minimise the missing data. A maximum dropout and/or missing data of 10% is anticipated. We will analyse the data according to the intention-to-treat principle. A complete case analysis will be used.

### Plans to give access to the full protocol, participant-level data and statistical code {31c}

The full anonymised dataset will be available upon request after completion and publication.

#### Composition of the data monitoring committee, its role and reporting structure {21a}

The study will be monitored by a certified individual from the research centre at the beginning (after the first inclusions) and at the end of the study. This person is not involved in this study and is therefore independent from the trial. This monitor will check the patients’ safety and whether the study is executed properly.

#### Adverse event reporting and harms {22}

Adverse events (AEs) are defined as any undesirable experience occurring to a subject during the study procedure, whether or not considered related to VR. All AEs reported spontaneously by the subject or observed by the investigator or his staff will be recorded.

A serious adverse event (SAE) is any untoward medical occurrence or effect that results in death, is life-threatening (at the time of the event), requires hospitalisation or prolongation of existing inpatients’ hospitalisation, results in persistent or significant disability or incapacity, is a congenital anomaly or birth defect or any other important medical event that did not result in any of the outcomes listed above due to medical or surgical intervention but could have been based upon appropriate judgement by the investigator. An elective hospital admission will not be considered as a serious adverse event.

The investigator will report the SAEs through the web portal ToetsingOnline to the accredited METC that approved the protocol, within 7 days of first knowledge for SAEs that result in death or are life-threatening followed by a period of a maximum of 8 days to complete the initial preliminary report. All other SAEs will be reported within a period of maximum of 15 days after the sponsor has first knowledge of the serious adverse events.

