If the child is assigned to the control group, the plaster procedure is then performed by the orthopaedic practitioner. If the child is assigned to the intervention group, the investigator starts the video of choice and places the VR goggles and headphones on the child’s head (adjusting the straps if necessary) before the plaster procedure is performed by the orthopaedic practitioner. During the plaster treatment, the child’s fastest heart rate is recorded by the investigator, using the finger pulse oximeter.

After the procedure, the VR goggles, headphones and finger pulse oximeter are removed. Hereafter, the child’s anxiety and pain scores are collected once more using the CFS^15^ and NRS pain. Additionally, the child and accompanying parent/guardian are asked to rate their satisfaction with the procedure, using the NRS satisfaction.

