#### Provisions for post-trial care {30}

There will be no separate insurance for subjects participating in this study. The risks associated are not increased, because regular treatment is used in both groups and the VR goggles are just used to distract patients. A request for dispensation from the statutory obligation to provide insurance has been approved. Cover for damage to research subjects through injury or death caused by this study is provided by the liability insurance of the Amphia Hospital.

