Recently, Jivraj et al. [13] have studied the effects of VR during plaster removal in a small general paediatric orthopaedic population. They found that the use of VR significantly reduced the child’s anxiety levels. However, there are a few differences in the study design compared with our study. Firstly, the VR set-up differs. Jivraj et al. [13] let the children play a video game with a manual controller, while the present study will show a short video. A video game with a manual controller will not be possible for the majority of our population, i.e. those with upper extremity fractures. Jivraj et al. [13] also mentioned that children under the age of seven found it hard to understand the game and would likely benefit more from a video experience. Secondly, another difference between the two studies is the population type and number. Jivraj et al. [13] included 90 patients with plaster removal for any indication, whereas the present study will include 270 patients in different phases of plaster treatment for fractures only. Due to this difference in population, both studies will provide valuable information on the anxiety-inducing effects of VR in the children treated in plaster room. Thirdly, the instruments to measure anxiety differ between the studies. Where this study uses the CFS and heart rate, Jivraj et al. [13] used the Short State Anxiety Inventory Scale (Short SAIS) for pre- and post-procedural anxiety measurements and the Children’s Emotional Manifestation Scale (CEMS) to measure the anxiety level during the procedure. While both methods are validated methods of measuring anxiety, the CEMS was found to be unpractical in a busy plaster room [13]. However, it will be interesting to study the effects of different methods of anxiety testing on the outcomes in future studies. Lastly, the secondary outcome measures differ between the studies. Jivraj et al. [13] recorded the Penn State Worry Questionnaire for Children (PSWQ-C) scores, nausea level and desire for future use of VR. The secondary outcomes and subanalyses in the present study will therefore add useful information to the knowledge of VR and its effects on outcomes. We believe our study can provide an important contribution to the understanding of children’s anxiety and the role of VR as a distraction method.

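### Adverse events are collected passively and only for the procedure itself, so a low count would be weak support for the statement that VR adds no risk

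*Protocol article*

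**What the plan says.** The section on adverse event reporting and harms {22} of the protocol article defines an adverse event as "any undesirable experience occurring to a subject during the study procedure, whether or not considered related to VR". It then sets the capture rule: "All AEs reported spontaneously by the subject or observed by the investigator or his staff will be recorded". The same rule applies to both arms.

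The intervention description {11a}, the outcomes {12} and the data collection plan {18a} list what the child is asked: the Child Fear Scale (CFS) and NRS pain before and after the procedure, and NRS satisfaction after it. No item on nausea, dizziness or a similar symptom is named. The section on missing data {20c} says that "all the data will be collected during the visit in the plaster room; there is no follow-up".

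Two passages state that VR adds no risk. The section on post-trial care {30}, explaining why there is no separate insurance, says "The risks associated are not increased, because regular treatment is used in both groups and the VR goggles are just used to distract patients". Section {20c}, explaining why few withdrawals are expected, says "the intervention is not invasive and does not increase the risks of the standard procedure".

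The Discussion notes that the earlier study of VR during plaster removal recorded "nausea level and desire for future use of VR", and lists this among the differences from the present trial.

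**The concern.** The effects a headset is most likely to cause are felt rather than seen. Under the stated rule, such a symptom enters the data only if a child volunteers it or someone in the room notices it. Four features make this rule a poor match for the intervention:

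- The inclusion criteria admit children from age 5, who may not volunteer a mild symptom.
- During the procedure, the VR child wears goggles and headphones, which makes both observation and conversation harder in that arm only.
- Section {17a} says nobody is blinded, and section {18a} says one individual collects all data. Detection may therefore differ by arm in either direction: lower under VR because the face is covered, or higher because the observer is alert to VR effects.
- The definition is limited to the procedure, so a symptom noticed once the goggles are off is not clearly covered.

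At stake is the tolerability information on a device that could become routine for young children. A short list of adverse events could reflect how they were collected and still be read as confirming that risk is not increased.

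**Working it through.** **The plan's own figures.** The plan states no figure for adverse events. The only relevant numbers are the group sizes in the sample size section {14}: SD 1.40, difference 0.5, power 80%, alpha 0.05. Taken as two-sided:

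n = 2 × (1.960 + 0.842)² × 1.40² / 0.5² = 123.07 per group

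This matches the stated 123. The plan then enrols 135 per group for 10% dropout (123 × 1.1 = 135.3; 123 / 0.9 = 136.7). The point does not depend on these figures; 135 serves only as the number of VR children.

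**Assumptions, none from the documents.** True symptom rate p in the VR arm: 5%, 10% or 15%. Control rate: 1%. Share captured c: 100%, 50% or 25%, equal in both arms.

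**Step 1: recorded cases in the VR arm.** Expected number = 135 × p × c. Chance of recording none = (1 − p × c)^135.

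| True rate p | Capture c | Expected recorded | Chance of none |
|---|---|---|---|
| 5% | 100% | 6.75 | 0.1% |
| 5% | 50% | 3.4 | 3% |
| 5% | 25% | 1.7 | 18% |
| 10% | 50% | 6.75 | 0.1% |
| 10% | 25% | 3.4 | 3% |
| 15% | 25% | 5.1 | 0.6% |

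**Step 2: power to see a difference between arms.** Two-sided Fisher test at 0.05, 135 per arm, by exact enumeration:

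| True rates, VR vs control | Full capture | Half | Quarter |
|---|---|---|---|
| 5% vs 1% | 0.34 | 0.07 | 0.005 |
| 10% vs 1% | 0.90 | 0.48 | 0.09 |
| 15% vs 1% | 0.996 | 0.83 | 0.32 |

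A 5% rate would be hard to separate from 1% even with full capture. At 10%, passive capture turns a good chance of detection into an even or poor one. At 15%, half capture still leaves 83% power.

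**Step 3: what zero events would show.** The exact two-sided 95% upper limit for 0 of m is 1 − 0.025^(1/m):

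- m = 135: 2.7% (the one-sided limit, 1 − 0.05^(1/135), is 2.2%)
- m = 123: 3.0% (one-sided 2.4%)

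These limits bound the rate of recorded symptoms. They bound the true rate only if capture is complete. At half capture, zero of 135 is compatible with a true rate up to 2.7% / 0.5 = 5.4%; at a quarter, up to 2.7% / 0.25 = 10.8%. Because the passive rule leaves c unknown, the reader cannot make this correction.

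**The case against.** The strongest reply is that this is a preference and not an error. The definition of an adverse event is broad, the rule is the same in both randomised arms, harm is not among the objectives or outcomes, and no comparison of adverse events is promised. The article is also condensed, and its questionnaires and case report form are not shown. Part of this stands: nothing is misstated, and the point is a modest one. But the capture rule is stated outright, so it can be assessed as a method.

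A reader might infer three stronger things that the documents do not support:

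- *That the no-added-risk statement cannot be tested.* Events are recorded under one rule in both arms and can be compared, with reduced and possibly unequal sensitivity. The 83% power for 15% vs 1% at half capture shows this.
- *That the trial sets out to show no added risk.* Sections {30} and {20c} use it as background reasoning, for insurance and for expected withdrawals. It is neither an objective nor a hypothesis.
- *That under-counting is certain, or that the trial will probably report no events.* No document gives a symptom or capture rate. Even at 5% true incidence and 25% to 50% capture, at least one case is recorded with probability 82% to 97%.

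Two further replies carry some weight. The goggles come off before the child is questioned with a parent or guardian present, so observation does not end with the procedure; still, the questions described do not cover symptoms. And the earlier study used a video game with a manual controller, and its nausea results are not given here. It shows that the authors knew such a measure had been used, and says nothing about the rate to expect in this trial.

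**Conclusion.** The concern holds in a limited form. Collection is passive and confined to the procedure, with no structured symptom question, so mild subjective symptoms are likely to be under-recorded, possibly unequally between unblinded arms. A low count would be weak support for the statements in sections {30} and {20c}.

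The size depends wholly on assumed rates. For 10% vs 1%, power falls from 0.90 with full capture to 0.48 at half and 0.09 at a quarter. These figures also assume equal capture in both arms and 135 children observed in each. The primary outcome, randomisation and sample size are untouched. This is a cheap improvement to the safety information and does not threaten the trial's main conclusion.

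**What to change.** At the end of the existing post-procedure questionnaire, after CFS, NRS pain and NRS satisfaction so that those answers cannot be affected, ask every child in both arms the same yes/no items: nausea, dizziness, headache. Record early removal of the goggles. Report counts by arm with exact two-sided 95% intervals, separately from spontaneously reported or observed events.

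The trial status section gives a start date of 21 January 2021. If the items are added after recruitment has begun, report prompted symptoms only for children enrolled after the change. Describe earlier events as passively collected, without concluding absence of harm. The bound then weakens: if, say, 67 of 135 VR children were asked and none reported a symptom, the upper limit would be 1 − 0.025^(1/67) = 5.4%. If no change is possible, the same wording about passive collection should cover the whole trial.

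The cost is a few seconds per child, one form item and an amendment. Prompting will raise the reported rate of mild symptoms in both arms; the control arm shows how much of that is background. The items would still miss symptoms that begin after the visit.

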#### Frequency and plans for auditing trial conduct {23}

We have no plans to audit the data.

#### Plans for communicating important protocol amendments to relevant parties (e.g. trial participants, ethical committees) {25}

Protocol modifications will be communicated to the relevant parties in the form of an amendment.

#### Dissemination plans {31a}

The results of this study will be presented at scientific meetings and published in a peer-reviewed medical journal.

## Discussion

The aim of this study is to evaluate the effect of distraction by virtual reality on the anxiety levels of children with fractures in the plaster room. Visual distraction with a smartphone or tablet and noise reduction with headphones both have shown a positive effect on the child’s anxiety in different clinical settings [2, 6, 7]. Moreover, VR has successfully reduced both pain perception and anxiety in children in other clinical situations and has proven to be more effective than a tablet [7–12]. Therefore, the combination of visual (with VR goggles) and auditory distraction (with headphones) is hypothesised to provide clear anxiety reduction in the paediatric orthopaedic trauma population described in this protocol.

Recently, Jivraj et al. [13] have studied the effects of VR during plaster removal in a small general paediatric orthopaedic population. They found that the use of VR significantly reduced the child’s anxiety levels. However, there are a few differences in the study design compared with our study. Firstly, the VR set-up differs. Jivraj et al. [13] let the children play a video game with a manual controller, while the present study will show a short video. A video game with a manual controller will not be possible for the majority of our population, i.e. those with upper extremity fractures. Jivraj et al. [13] also mentioned that children under the age of seven found it hard to understand the game and would likely benefit more from a video experience. Secondly, another difference between the two studies is the population type and number. Jivraj et al. [13] included 90 patients with plaster removal for any indication, whereas the present study will include 270 patients in different phases of plaster treatment for fractures only. Due to this difference in population, both studies will provide valuable information on the anxiety-inducing effects of VR in the children treated in plaster room. Thirdly, the instruments to measure anxiety differ between the studies. Where this study uses the CFS and heart rate, Jivraj et al. [13] used the Short State Anxiety Inventory Scale (Short SAIS) for pre- and post-procedural anxiety measurements and the Children’s Emotional Manifestation Scale (CEMS) to measure the anxiety level during the procedure. While both methods are validated methods of measuring anxiety, the CEMS was found to be unpractical in a busy plaster room [13]. However, it will be interesting to study the effects of different methods of anxiety testing on the outcomes in future studies. Lastly, the secondary outcome measures differ between the studies. Jivraj et al. [13] recorded the Penn State Worry Questionnaire for Children (PSWQ-C) scores, nausea level and desire for future use of VR. The secondary outcomes and subanalyses in the present study will therefore add useful information to the knowledge of VR and its effects on outcomes. We believe our study can provide an important contribution to the understanding of children’s anxiety and the role of VR as a distraction method.

## Trial status

This trial commenced on 21 January 2021. The anticipated end date of the study is 1 April 2022

## Data Availability

Only the investigators will have full access to the final dataset.

## Abbreviations

AE: Adverse event
CFS: Child Fear Scale
EDC: Electronic data capture
MEC-U: Medical research Ethics Committees United (one of the METCs)
METC: Medisch Ethische Toetsing Commissie (in English: Medical Ethics Review Committee)
NRS: Numeric Rating Scale
NYPD: New York Police Department
SAE: Serious adverse event
VR: Virtual reality
